#### Clinical procedures to measure metabolic function

For the OGTT, each subject consumes a 75-g oral glucose load within 5 min. Blood samples are collected immediately before and 10, 30, 60, 90 and 120 min after glucose ingestion for measurement of serum glucose and insulin. Blood for serum glucose determination is collected with sodium fluoride and blood for serum insulin is collected with heparin. Assays are performed in the UAB Human Physiology and Metabolism Core. Serum glucose, insulin, and C-peptide values are analyzed for measures of insulin sensitivity and β-cell (cells that control insulin secretion in the pancreas) function using mathematical modeling techniques developed for data generated from the OGTT [52]. Whole body insulin sensitivity (WBIS) is also calculated using the Matsuda index (a formula based on insulin and glucose values measured during the OGTT) [57]. The HOMA-IR is calculated using the following formula: HOMA-IR = $$ \frac{\mathrm{glucose}\ \left(\mathrm{mg}/\mathrm{dL}\right)\times \mathrm{insulin}\ \left(\upmu \mathrm{U}/\mathrm{mL}\right)}{405} $$ [58]. Serum glucose and C-peptide assays are performed on an automated analyzer (Sirrus analyzer; Stanbio Laboratory, Boerne, TX) and serum insulin is measured using an immunofluorescent method with an AIA-600 II analyzer (TOSOH Bioscience, South San Francisco, CA) per the manufacturers’ instructions.

For lipid analysis, venous blood samples are collected to measure the participant’s total cholesterol, triglycerides (TG), high-density lipoprotein cholesterol (HDL-C), and low-density lipoprotein cholesterol (LDL-C) levels in the fasting state. This blood is drawn using the catheter that is placed for the OGTT so it does not require an extra needle stick. Total cholesterol, HDL-C, and TG are measured with the Sirrus analyzer. LDL-C levels are estimated using the formula LDL-C = total cholesterol − HDL-C − triacylglycerol/5 [59]. Analyses are performed in the UAB Human Physiology and Metabolism Core.

#### Clinical procedures to measure body composition

We use dual-energy x-ray absorptiometry (DXA) to measure body composition. Total body imaging (to measure total fat and lean mass and visceral fat mass) is acquired using the GE Healthcare Lunar iDXA (GE Healthcare Lunar, platform version 16, Madison, WI) and analyzed using enCORE software version 13.6 in the UAB Human Physiology and Metabolism Core. Daily quality-control scans are acquired during the study period. Participants are scanned using our standard imaging and positioning protocols used both in able-bodied individuals [60, 61] and the SCI population [62] . Participants are placed on the center of DXA scanner in a supine position with the arms facing medially thumbs-up. The legs are strapped to secure the knees and feet to prevent movement during the scan. For measuring visceral fat, a region of interest is automatically defined, with the caudal limit placed at the top of the iliac crest and the height set to 20% of the distance from the top of the iliac crest to the base of the skull to define the cephalad limit. Fat mass data from DXA are transformed into CT adipose tissue volume using a constant correction factor (0.94 g/cm^3^) [63]. This constant is generally consistent with the density of adipose tissue.

#### Procedures to measure changes in the composition of gut bacteria

Gut bacterial (microbial) composition patterns are determined from stool samples using our established protocol [64]. Stool collection occurs at participants’ homes. Participants or their caregivers are provided with a prepaid and labeled FedEx package containing a stool collection kit (Para-pak vial for sample preservation, stool collection container, 2-gal Ziploc bag for disposal of collection container, and sanitizing wipes). After bowel movement, approximately 5–10 mL of stool is transferred to the Para-pak vial using the attached spatula. For participants who have their bowel management program on their beds, the stool collection container is not used. Fedex packages containing stool samples are shipped to our laboratory using the overnight shipping option to ensure appropriate preservation of the microbiota. Upon delivery, the fecal samples are diluted in Cary-Blair medium to 0.1 mg/mL for a total volume of 20 mL with 10% by volume glycerol. Aliquots of 200 μL are stored at −80 °C for DNA extraction/gut bacteria analysis. Fecal DNA is isolated via a Fecal DNA Isolation Kit. The 16S rRNA gene amplification protocol with the MiSeq System is used to characterize the composition of gut bacteria to the family level, and in some cases the genus and species level [64]. The relative abundance of identified organisms is normalized prior to analysis based on maximum read counts per sample. The organisms with low relative frequencies (< 0.1%) are filtered. The remaining organisms are used for within-subject and between-subject comparison analyses.

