### Outcome measures and analysis

#### Primary outcomes

The primary outcomes are as follows: 1) metabolic function (glucose tolerance, insulin sensitivity, β-cell function and lipid profile); 2) body composition (total fat mass, total lean mass and visceral fat mass)l; and 3) gut microbiome (composition of gut bacteria).

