### Statistical analysis

All data analyses will be carried out using data from participants that complete the study intervention. Descriptive statistics will be calculated for all study parameters of interest. Analyses for all aims include comparisons of means of outcome measures, which include the Matsuda index (insulin sensitivity), 2-h OGTT serum glucose levels (glucose tolerance), β-cell function, total cholesterol, TG, LDL-C, and HDL-C, total lean mass, total fat mass, visceral fat mass, and composition of gut bacteria between the two groups (LC/HP diet and control diet) as well as comparisons within each group of the changes from the baseline visit to the week 8 visit. The primary method of analysis is mixed models repeated measures analyses, such as repeated measures analysis of covariance. An appropriate structure for the covariance matrix (e.g., the unstructured covariance matrix) will be selected for these models using the final data. This method allows us to compare changes over time (8 weeks) and differences between groups simultaneously. Potential confounders, such as age, gender, injury level, time since injury, and levels of physical activity, will be accounted for in these analyses. Overall adjusted comparisons between groups at baseline will be performed using the two-group *t* test, and overall unadjusted comparisons of the change from the baseline visit to the week 8 visit is performed using the paired *t* test. If assumptions of normality of distribution for the above tests are not tenable, variables may be log10 transformed prior to analysis or appropriate nonparametric tests such as the Wilcoxon rank-sum and signed-rank tests may be used. Generalized linear model techniques, such as regression analyses and mixed models repeated measures analyses, will be used to determine how changes in composition of gut bacteria are associated with improvements in metabolic function, or how improvements in metabolic function are related to improvements in quality of life. Secondary analysis of participants who have type 2 diabetes or glucose intolerance will be performed if the numbers of participants with these conditions differ greatly between the study groups. If we have missing data at study completion, we will not perform multiple imputation or apply the last observation carried forward method; instead, we will perform a secondary analysis of participants who completed the study versus participants who did not complete the study and determine if these two groups differ in any substantial way. Statistical tests will be two-sided and performed using a 5% significance level. SAS software, version 9.4 or later, will be used to conduct the statistical analyses.

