New and insightful information to be derived from this project will include: 1) development of a low-cost, simple, self-administered LC/HP dietary intervention for improving metabolic function in individuals with chronic SCI; 2) demonstration of the efficacy of a LC/HP diet as a nonpharmacological option for improving blood glucose control, insulin sensitivity, β-cell function, and whole body and regional body composition; 3) improved understanding of the composition of gut bacteria in SCI and how a LC/HP dietary intervention alters gut bacteria composition; 4) increased knowledge of the influence of gut bacteria on metabolic function in SCI; and 5) improved understanding of the relationship between metabolic function and quality of life in individuals with long-standing SCI.

In conclusion, there are several innovative features of the proposed experiments that are expected to significantly advance the field and improve metabolic function, with the overall goal of reducing metabolic disease risk among individuals with long-standing SCI. A dietary intervention that results in improvements in metabolic function can be implemented anywhere in the world at low cost and without major regulatory hurdles. Better metabolic function in individuals with SCI will contribute to a significantly higher quality of life as well as improved long-term health outcomes.

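### The gut-bacteria primary outcome has no single deciding test and no false-discovery control, and its organisms come under a flat two-sided 5% level

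*Protocol article*

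**What the plan says.** All references are to the protocol article.

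- **Primary outcomes** lists gut microbiome composition third, beside metabolic function and body composition.
- **Procedures to measure changes in the composition of gut bacteria** says sequencing is used "to characterize the composition of gut bacteria to the family level, and in some cases the genus and species level". Then: "The organisms with low relative frequencies (< 0.1%) are filtered". Then: "The remaining organisms are used for within-subject and between-subject comparison analyses".
- **Statistical analysis** states: "Analyses for all aims include comparisons of means of outcome measures". Gut-bacteria composition is in the list of measures that follows, for between-group and within-group comparison. The methods named are mixed models, t tests and, as fallback, log transformation or Wilcoxon tests. Regression and mixed models "will be used to determine how changes in composition of gut bacteria are associated with improvements in metabolic function". The error rule is: "Statistical tests will be two-sided and performed using a 5% significance level". No exception is made for the organisms.
- **Power calculations** says that none could be done for gut-bacteria composition.
- **Discussion** counts among the expected contributions "improved understanding of the composition of gut bacteria in SCI and how a LC/HP dietary intervention alters gut bacteria composition".

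**The concern.** Composition is a set of abundances, one per organism. The methods named in the Statistical analysis section are ordinarily applied to one number per participant and visit. To use them, the analyst must either test organisms separately or first reduce the set to one index or distance. The outcome and analysis sections name no index, distance or community test, and the plural organisms are what is sent into the comparisons.

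If organisms are tested separately under the stated level, one listed primary outcome becomes a family of tests with no control inside it. Ranking the three primary domains, or splitting alpha between them, would not cure this, because the multiplicity lies within one domain. A trial with no diet effect on gut bacteria could then report that particular organisms changed. Nothing in the article marks such results as exploratory.

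**Working it through.** **Inputs from the article.** Significance level 5%, two-sided (Statistical analysis). Final size 30 per group (Power calculations). Organisms kept: those at or above 0.1% relative frequency, number not stated.

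**Assumptions.** Number of organisms m from 10 to 80. Pairwise correlation ρ of the test statistics from 0 to 0.5. No diet effect on any organism. Only between-arm tests are counted; the planned within-group tests would add to the risk.

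**The plan's own figures.** The article gives no error rate or power for gut bacteria, so there is none to reproduce. Its metabolic power figures do reproduce at unadjusted two-sided 5% with 30 per group. By the exact two-group t test, power is 80.1% for 2.8 Matsuda units (SD 3.8) and 80.2% for 11.8 mg/dL (SD 16), against a stated 80%.

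**Step 1, independent organisms.** P(at least one false difference) = 1 − 0.95^m.

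- m = 10: 1 − 0.5987 = 40.1%
- m = 13: 48.7%
- m = 14: 51.2%, the first value above one half
- m = 20: 1 − 0.3585 = 64.2%
- m = 40: 1 − 0.1285 = 87.1%

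**Step 2, correlated organisms.** With one common factor u and c = 1.96,

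P = 1 − ∫ [Φ((c − √ρ·u)/√(1−ρ)) − Φ((−c − √ρ·u)/√(1−ρ))]^m φ(u) du.

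| m | ρ = 0 | ρ = 0.2 | ρ = 0.3 | ρ = 0.5 |
|---|---|---|---|---|
| 10 | 40.1% | 37.7% | 35.1% | 28.7% |
| 14 | 51.2% | 47.5% | 43.8% | 34.8% |
| 20 | 64.2% | 59.0% | 54.0% | 41.9% |
| 40 | 87.1% | 80.8% | 74.5% | 57.1% |
| 80 | 98.3% | 95.2% | 90.9% | 72.9% |

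The 50% mark is passed at m = 14 for ρ = 0, at m = 18 for ρ = 0.3 and at m = 30 for ρ = 0.5. With stronger correlation the risk drops further: at ρ = 0.8, 20 organisms give 22%.

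**Step 3, expected count.** The expected number of false differences is 0.05 × m whatever the correlation: 1 in 20 organisms, 2 in 40.

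**Step 4, relative abundances.** Proportions sum to one, so the organisms are not strictly independent. A simulation of 3,000 trials used 30 per arm, log-normal abundances scaled to proportions and a t test on the change in log abundance. With no diet effect, about 60% of trials with 20 organisms and 86% with 40 had at least one p < 0.05. This is close to the independent case.

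**Step 5, with control.** Benjamini-Hochberg at 5% brought the chance of any false organism to about 5% in the same simulation. In a separate run with equally correlated statistics it was 4% to 5% for 10 to 50 organisms at correlations 0 to 0.5.

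**The case against.** The strongest reply is that the article never says organisms are tested singly. Filtered organisms could equally feed a community measure. Composition appears once, as a single item, in the list of measures, and the Discussion speaks of bacterial diversity as something the diet should improve. A general 5% level is also compatible with a global test at 5%, or with adjusted values judged at 5%. The choice of community metric or false-discovery method is detail that a condensed article may leave to an analysis plan that is not shown.

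Much of this stands, and it limits the claim. A reader might infer three stronger things that the article does not support:

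- **That it prescribes 5% for each organism.** The word each is not there. Single-organism testing is the natural reading of the named methods together with the plural organisms, but it remains an inference.
- **That a false finding is more likely than not as long as organisms are weakly correlated.** This also needs enough organisms. With 10 it is about 40% even if they are independent, and the number is undocumented.
- **That every organism will be regressed on every metabolic measure.** Crossing 20 organisms with seven measures would make 140 tests and about 7 false positives (140 × 0.05). The article plans models linking change in composition to metabolic improvement and does not fix that grid.

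The consequence should not be inflated either. The Discussion calls the bacterial profiles preliminary and promises better understanding here, while its wording about demonstrating efficacy is kept for metabolic and body-composition measures.

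What the reply does not remove is that a primary outcome is given one-number methods and an unqualified 5% level without the number being named. The Discussion's mention of diversity defines no measure. If a single index was intended, it still has to be identified.

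**Conclusion.** The point holds in conditional form. As published, the test that decides the gut-bacteria primary outcome is not identified, and the natural reading of the stated methods and level leaves organism-level comparisons uncontrolled. Under that reading, with 10 to 40 organisms and no diet effect, the chance of at least one false between-arm difference is 40% to 87% if organisms are independent and 29% to 57% at correlation 0.5. Even the lowest of these is nearly six times 5% (28.7 / 5 = 5.7). These sizes rest on an assumed number of organisms and an assumed correlation, neither of which the article gives. The change should be made, but it is not a fatal defect. Confidence is medium because the unit of testing is inferred and an unseen analysis plan might already settle it.

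**What to change.** In the Statistical analysis section:

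1. Name one between-arm community-level test at two-sided 5% as deciding the gut-bacteria outcome. One option is a permutation test of the arm-by-visit interaction on between-sample distances, permuting arm labels across participants. Another is a between-arm comparison of one diversity index named in advance. Each participant's own baseline-to-week-8 distance would not serve alone: it measures the size of a shift and not its direction, so equal-sized shifts in different directions would be missed.
2. Report organism-level between-arm comparisons with Benjamini-Hochberg control at 5% across all organisms kept at each taxonomic level.
3. Label within-arm organism comparisons, and any organism-level associations with metabolic outcomes, as exploratory, with false-discovery-adjusted values.
4. Word the general 5% statement so that it refers to these rules.

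The cost is a few sentences, routine code and the approvals required under Protocol amendments. No participants or samples are added. The downside is lower power per organism, so fewer individual organisms will be declared significant.

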#### Secondary outcome

The secondary outcome is health-related quality of life (QOL). This is measured via the SCI-QOL measurement system, which consists of a set of items that have been developed specifically for use in spinal cord medicine [65, 66]. Two scales that measure physical and health-related QOL are being used (Table 1).

**Table 1 Tab1:** List of spinal cord injury quality of life (SCI-QOL) questionnaire domains and items used in the study

Physical–medical health	
Pressure ulcers	
Bladder management difficulties	
Bladder complications	
Bowel management difficulties	
Pain interference	
Pain behavior	
Physical function	
Basic mobility	
Ambulation	
Fine motor	
Self-care	
Wheelchair mobility	

### Statistical analysis

All data analyses will be carried out using data from participants that complete the study intervention. Descriptive statistics will be calculated for all study parameters of interest. Analyses for all aims include comparisons of means of outcome measures, which include the Matsuda index (insulin sensitivity), 2-h OGTT serum glucose levels (glucose tolerance), β-cell function, total cholesterol, TG, LDL-C, and HDL-C, total lean mass, total fat mass, visceral fat mass, and composition of gut bacteria between the two groups (LC/HP diet and control diet) as well as comparisons within each group of the changes from the baseline visit to the week 8 visit. The primary method of analysis is mixed models repeated measures analyses, such as repeated measures analysis of covariance. An appropriate structure for the covariance matrix (e.g., the unstructured covariance matrix) will be selected for these models using the final data. This method allows us to compare changes over time (8 weeks) and differences between groups simultaneously. Potential confounders, such as age, gender, injury level, time since injury, and levels of physical activity, will be accounted for in these analyses. Overall adjusted comparisons between groups at baseline will be performed using the two-group *t* test, and overall unadjusted comparisons of the change from the baseline visit to the week 8 visit is performed using the paired *t* test. If assumptions of normality of distribution for the above tests are not tenable, variables may be log10 transformed prior to analysis or appropriate nonparametric tests such as the Wilcoxon rank-sum and signed-rank tests may be used. Generalized linear model techniques, such as regression analyses and mixed models repeated measures analyses, will be used to determine how changes in composition of gut bacteria are associated with improvements in metabolic function, or how improvements in metabolic function are related to improvements in quality of life. Secondary analysis of participants who have type 2 diabetes or glucose intolerance will be performed if the numbers of participants with these conditions differ greatly between the study groups. If we have missing data at study completion, we will not perform multiple imputation or apply the last observation carried forward method; instead, we will perform a secondary analysis of participants who completed the study versus participants who did not complete the study and determine if these two groups differ in any substantial way. Statistical tests will be two-sided and performed using a 5% significance level. SAS software, version 9.4 or later, will be used to conduct the statistical analyses.

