### Power calculations

Power calculations were performed using nQuery Advisor + nTerim 3.0 and assumed a two-sided statistical test and a significance level of 5%. We obtained estimates of the standard deviation (SD) for two clinically important metrics of metabolic function: a Matsuda index (indicator of insulin sensitivity) of 3.8 units [33], and 2-h OGTT serum glucose levels of 16 mg/dL [44]. Given the dearth of publications related to the effects of diet composition on gut bacteria, we were unable to perform power calculations for gut bacteria composition; however, we have adequate power to detect statistically significant differences in primary metabolic outcomes.

As described in Fig. 4, we intend to recruit 100 participants (50 per group) for the study, taking into account an estimated final participation rate of 80% and an attrition rate of 20%. With a final sample size of 30 participants per group (LC/HP diet and control), and also assuming a two-group *t* test and the prior assumptions, we have 80% power to detect between-group differences of 2.8 units in the Matsuda index, and 11.8 mg/dL in 2-h OGTT serum glucose levels as being statistically significant. With this same sample size, and also assuming a paired *t* test and the prior assumptions, we have 80% power to detect within-group differences of 2.1 units in the Matsuda index and 8.5 mg/dL in 2-h OGTT serum glucose levels as being statistically significant. We believe that these estimates are conservative because we will be performing our primary statistical analyses for between-group and within-group comparisons simultaneously using statistical methods that are more sophisticated than those that are assumed here.

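### Within-group changes share primary standing with the between-group comparison, no single between-arm contrast is named as the efficacy test, and a baseline t test is mislabelled as adjusted

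*Protocol article*

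**What the plan says.** Under Power calculations, the protocol gives detectable differences at 80% power with 30 participants per group, both between groups (two-group t test: 2.8 Matsuda units, 11.8 mg/dL in 2-h glucose) and within a group (paired t test: 2.1 units, 8.5 mg/dL). It calls these conservative because the investigators will be "performing our primary statistical analyses for between-group and within-group comparisons simultaneously" with more sophisticated methods.

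Under Statistical analysis, the comparisons for all aims are between-group means together with "comparisons within each group of the changes from the baseline visit to the week 8 visit". The primary method is a mixed model for repeated measures, with repeated-measures analysis of covariance as the example and an unstructured covariance matrix as a possible structure. It is said to address change over time and group differences at once. On covariates: "Potential confounders, such as age, gender, injury level, time since injury, and levels of physical activity, will be accounted for in these analyses". Two simpler tests follow. The first reads "Overall adjusted comparisons between groups at baseline will be performed using the two-group" t test. The second is an unadjusted paired t test of change from baseline to week 8.

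Under Study design and participants, eligibility rests on an OGTT: 2-h glucose of at least 140 mg/dL (impaired tolerance or diabetes), or a Matsuda index below 4.3 (insulin resistance).

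**The concern.** A randomised control arm exists so that change in the diet arm can be set against change without the diet. A pre-post test within the diet arm discards that protection. It responds to anything that moves both arms: regression to the mean, familiarity with the test, season, or the attention that comes with taking part. Regression to the mean is a particular risk here because entry requires an abnormal OGTT value and OGTT values are then the outcomes.

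If within-group and between-group results have equal standing, a report can say that the diet arm improved significantly and the control arm did not, and have this read as efficacy when the arms do not differ.

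Two further gaps add to this. A two-visit repeated-measures model yields several between-arm quantities: the group-by-time contrast, the week-8 difference, and a group effect averaged over both visits. The text does not choose among them, and their power differs widely. The baseline comparison is called adjusted but uses a test that adjusts for nothing, and in a randomised trial such a test is not evidence on efficacy.

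**Working it through.** **Inputs from the protocol (Power calculations).** Two-sided 5% level; 30 per group; SDs of "a Matsuda index (indicator of insulin sensitivity) of 3.8 units" and "2-h OGTT serum glucose levels of 16 mg/dL".

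**Inputs assumed.** The baseline to week-8 correlation ρ is not given, so 0.3, 0.5 and 0.7 are used. For the within-group test the plan's SD is taken as the SD of change, as the plan itself does.

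**1. The plan's own figures** (noncentral t).
- Two-group test, standard error SD × √(2/30): power is 80.1% at 2.8 Matsuda units and 80.2% at 11.8 mg/dL. Both reproduce.
- Paired test, standard error SD/√30: power is 80.3% at 8.5 mg/dL, which reproduces. At 2.1 Matsuda units power is 83.3%; 80% is reached at 2.01. The stated 2.1 is slightly conservative and plays no part in this point.

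**2. Within-group tests when the diet does nothing.** Let both arms truly change by the same amount m, and let p be the power of the paired test in one arm. The arms are independent, so the chance that only the diet arm is significant is p(1 − p). The standard error is 3.8/√30 = 0.694.

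| Common change m (Matsuda units) | m/0.694 | p | p(1 − p) |
|---|---|---|---|
| 1.0 | 1.44 | 0.286 | 0.204 |
| 1.5 | 2.16 | 0.552 | 0.247 |
| 2.1 | 3.03 | 0.833 | 0.139 |

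The diet arm is thus significant in 29% to 83% of trials, and it alone in 14% to 25%, with no difference between arms.

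**3. Which between-arm contrast.** With two visits, complete data and outcome variance σ², the per-participant variance is:
- difference in change scores: 2σ²(1 − ρ);
- ANCOVA on baseline: σ²(1 − ρ²).

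The ratio of the second to the first is (1 + ρ)/2.

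| ρ | Change score (×σ²) | ANCOVA (×σ²) | Ratio |
|---|---|---|---|
| 0.3 | 1.40 | 0.91 | 65% |
| 0.5 | 1.00 | 0.75 | 75% |
| 0.7 | 0.60 | 0.51 | 85% |

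The differences detectable with 80% power at 30 per arm follow by replacing SD with SD√(1 − ρ²) or SD√(2(1 − ρ)):

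| ρ | Matsuda: ANCOVA | Matsuda: change | 2-h glucose: ANCOVA | 2-h glucose: change |
|---|---|---|---|---|
| 0.3 | 2.67 | 3.31 | 11.23 | 13.93 |
| 0.5 | 2.42 | 2.80 | 10.19 | 11.77 |
| 0.7 | 2.00 | 2.17 | 8.41 | 9.12 |

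A simulation of 4,000 trials per setting, with a true effect of 2.8 Matsuda units at week 8, gave these powers at ρ = 0.3, 0.5 and 0.7:
- ANCOVA: 0.84, 0.89, 0.97;
- difference in change: 0.66, 0.80, 0.95;
- group effect averaged over both visits: 0.41, 0.36, 0.34.

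Type I error was about 5% for all three. They are all valid tests of no effect, but they are not interchangeable.

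**The case against.** The case for the plan is substantial, and most of it stands.

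- **Baseline adjustment is not excluded.** A reader might infer that the plan omits the baseline outcome value and can never arrive at a baseline-adjusted comparison. The text does not support that. The covariate list is introduced by *such as* and is open. In a repeated-measures model the baseline value can be one of the responses, and leaving it out of the covariates is then correct. The group-by-time contrast is valid, and with a common baseline mean it is essentially the baseline-adjusted week-8 difference. A full protocol or analysis plan, not shown, may fix the contrast.
- **No sentence says that a within-arm change alone establishes efficacy.** The Discussion frames the question as diet versus control, and the paired t test is listed apart from the primary method. It remains true that the power section gives within-group comparisons primary standing and their own 80% power.
- **Regression to the mean cannot be sized from the documents.** A reader might take the paired test at 8.5 mg/dL (80%) as the false-signal rate. That would pair the plan's SD of 16 with a source population that the protocol does not describe. Suppose a source mean of 130 and SD of 35, selection at 140 and above, the screening OGTT as baseline, and a retest correlation of 0.7. The mean of those selected is then 164.6 and the expected fall is 0.3 × 34.6 = 10.4 mg/dL. The SD of change is 25.7, and the paired test is significant about 57% of the time (71% at correlation 0.6, 40% at 0.8). Participants who enter on the Matsuda index alone would reduce the fall in glucose further. Whether the screening OGTT is also the baseline is itself an assumption.
- **Glycaemic category.** A reader might infer that it is wrongly left to chance imbalance. The sentence concerned describes a secondary analysis that "will be performed if the numbers of participants with these conditions differ greatly between the study groups"; it does not restrict the covariates. Randomisation is not described as stratified by category, so adjusting for it is a preference.
- **The word adjusted** may be a slip for unadjusted, as in the clause that follows it. No efficacy result depends on it, but the text is wrong as printed.

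**Conclusion.** The point holds in a limited form. The protocol gives within-group changes primary standing next to the between-group comparison, does not designate the between-arm contrast that decides efficacy, and mislabels a baseline t test. The model it names allows the right test.

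If the within-group results were read as efficacy, a diet-only significant change would appear in about 14% to 25% of trials with equal change in both arms. This rests on common changes of 1.0 to 2.1 Matsuda units, SD of change 3.8, 30 per arm and independent arms; it needs no assumption about what causes the common change. The efficiency gain from the baseline-adjusted contrast depends on an assumed correlation. It is clear at 0.3 (2.67 against 3.31 units detectable) and modest at 0.7 (2.00 against 2.17).

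None of the stated sample-size figures is wrong on this account. The correction is worth making, but it is a matter of specification and does not make the trial invalid.

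**What to change.** 1. For each outcome, name one between-arm contrast as the sole efficacy test: the week-8 difference from ANCOVA with the baseline value of that outcome as covariate or, essentially equivalent, a mixed model with a common baseline mean and unstructured covariance.
2. Report within-group changes descriptively, with confidence intervals and no efficacy claim, and amend the power section so that they no longer count among the primary analyses.
3. Delete the baseline t test, or relabel it as an unadjusted description of the arms.
4. Optionally, prespecify glycaemic category as a covariate.

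The cost is wording only. The baseline and week-8 values are already collected, and power at 30 per arm is kept or improved.
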